### Recruitment

All patients receiving OAT treatment from included clinics will be considered the reference target population. As part of an annual clinical assessment of patients receiving OAT linked to the ATLAS4LAR project [18], patients will receive information about the study and will be asked for consent to participate. All patients in the target population with inclusion and no exclusion criteria will be offered study participation until the targeted sample size has been reached. Participants giving informed consent will receive an extended clinical assessment, and be randomised for the study.

### Allocation and blinding

We will use a 1:1 randomisation ratio between the intervention and the control arm. Randomisation will be electronically registered. Blinding of patients is regarded as infeasible and patients will be informed about the follow-up they will receive. However, they will not receive information on follow-up in the other arm or the exact hypotheses for the study. The study will blind outcomes assessor.

### Data collection and management

Details on data collection and follow-up are given in Table 1*and* Fig. 1. Research nurses at the OAT clinics will measure/collect the primary outcome measures by blood samples and through interviews with all participants.

**Table 1 Tab1:** Study flow chart presenting follow-up visits and assessments at each visit

	Screening (research nurse)	Treatment follow-up week 0 to 16 (nurses/social workers)	Intervention assessment week 16 (12–16 after initiation)	Intervention post-assessment (10–30 weeks after completion of intervention)
**Research nurse assessment**	X		X	X
- Informed consent	X			
- Eligibility assessment	X			
- Follow-up by OAT staff		X		
- Clinical assessment	X		X	
Biochemical tests	X		X	X
Physical funct. (4-min step-test)	X		X	X
Full blood count, ferritin etc	X		X	X
SCL-10 (mental health)	X		X	X
FSS-3 (fatigue symptoms)	X		X	X
EQ-5D-5L (quality of life)	X		X	X

**Fig. 1 Fig1:**
[figure not shown]
The figure gives an overview of the timing of the intervention and follow-up for the study. * The arrows are indications of when the various measurements are timed

### Analyses and statistical methods

A detailed analysis plan will be developed before data export and data analysis. Analysis methods will be conducted in line with the CONSORT and SPIRIT guidelines as far as possible [19–21]. Two-sided tests will be used, and *p* < 0.05 will be used as the statistical significance threshold. Descriptive tables for the participants will be presented with categorical variables that will be summarized with percentages, and for continuous variables as medians with interquartile ranges, or means with standard deviation for continuous variables with a Gaussian distribution. The main outcomes will be analysed with linear mixed models. Efficacy estimates of the outcomes will be presented with 95% confidence intervals. If there are substantial imbalances in potential confounders at baseline, estimates with adjustments for these will be presented in sensitivity analyses. For missing data, appropriate imputations based on pre-defined assumptions and analysis plan will be done when necessary.

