### Outcomes

The primary outcome is psychological distress assessed with the Norwegian validated translation of the ten-item version of the Hopkins Symptom Checklist (SCL-10) in the mid of the intervention period 16 weeks after initiation (12–16) [13]. This will be evaluated with the mean SCL-10 item score and compared between the intervention and control arms.

Secondary outcomes are also measured at the same time 16 weeks after initiation and include the following:

Changes in fatigue assessed with the Fatigue Symptom Scale (FSS-3) [14]Physical functioning assessed with a 4-minute step-test that measures the number of steps climbed in 4 minutes [15]Changes in health-related quality of life assessed with the five dimensions and five level EuroQoL scale (EQ-5D-5L), as well as a self-reported question on happiness with a 0 to 10 visual analogue scale [16]Change in biochemical indicators of inflammation (compared to baseline estimates)All participants: Mean concentration of C-reactive protein in serum and total leukocyte count in bloodRandomized sub-group (*n* = 60, 1:1 intervention:control arm): IFN-gamma, IL-1beta, IL-1RA, IL-6, IL-8, IL-10, IL-17A, MCP-1, TNF-alfa measured in dried blood spotsBiochemical indicators of fruit intake (compared to baseline estimates)All participants: Folic acid levelsRandomized sub-group (*n* = 60, 1:1 intervention:control arm): carotenoids (vitamin A-related compounds) measured in dried blood spots

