### Sample size

We calculated sample sizes for a two-sample means test based on the following assumptions:The power is set at 90% with a two-sided alpha (α) error of 5%.Mean SCL-10 score in the control arm is 2.2 (SD: 0.8). This is based on data from a similar cohort [17].Mean SCL-10 score in the intervention arm is 1.90 (SD: 0.8).Intervention:control ratio of 1:1.

Based on the above-mentioned assumptions, 302 persons are required (151 in the intervention arm and 151 persons in the control arm). Statistical power was calculated in Stata SE 17.0.

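### The article's only covariate-adjustment rule is triggered by observed baseline imbalance, and nothing commits the primary mixed model to the screening SCL-10

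*Protocol article*

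**What the plan says.** All references are to the protocol article.

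- **Analyses and statistical methods**, on the model: "The main outcomes will be analysed with linear mixed models". The fixed effects, the random effects and the role of the screening score are not given.
- **Same section**, on adjustment: "If there are substantial imbalances in potential confounders at baseline, estimates with adjustments for these will be presented in sensitivity analyses". This is the only statement on covariates.
- **Same section**, on what follows later: "A detailed analysis plan will be developed before data export and data analysis".
- **Outcomes**, on the primary outcome: "This will be evaluated with the mean SCL-10 item score and compared between the intervention and control arms". The time point is about 16 weeks after initiation, and the outcome is not worded as a change from baseline.
- **Data collection and management, Table 1**: SCL-10, FSS-3, EQ-5D-5L, the step-test and the biochemical tests are scheduled at screening, at week 16 and at the post-intervention assessment.
- **Sample size**: "We calculated sample sizes for a two-sample means test based on the following assumptions". The inputs are means of 2.2 and 1.90, SD 0.8 in both arms, 90% power, two-sided 5% and a 1:1 ratio. The result is 151 per arm, 302 in all, with no baseline covariate in the calculation.

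**The concern.** In an individually randomised trial, baseline imbalance arises by chance. The case for adjusting for a variable rests on how strongly it predicts the outcome, and that can be judged before any data are seen. A rule that waits for imbalance uses the wrong criterion. Here it is also undefined, since neither the size of a substantial imbalance nor the list of candidate variables is fixed. Whether adjusted estimates appear, and for which variables, would be settled after the baseline table has been seen.

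The screening value of the outcome is usually one of its best predictors, and this trial collects it anyway. Yet the only adjustment rule would place it, at most, in a sensitivity analysis. Naming linear mixed models does not settle the matter, because such a model may or may not draw on the screening score. At stake are the width of the primary confidence interval and how far a chance difference in baseline distress stays in the headline estimate.

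**Working it through.** **Inputs.** From Sample size: difference δ = 2.2 − 1.90 = 0.30, SD = 0.8, two-sided α = 0.05, power 90%, 151 per arm. Not in the article: the correlation r between screening and week-16 SCL-10. A range of 0.3 to 0.7 is assumed.

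**Step 1. Reproduce the stated sample size.** Normal approximation: n per arm = 2(1.960 + 1.282)² × 0.8² / 0.30² = 149.4, so 150 per arm and 300 in all. The t-test version gives 150.4, so 151 per arm and 302 in all, which is the article's figure. Power at 151 per arm is 90.3% (normal) or 90.1% (t).

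**Step 2. Precision without baseline.** SE = 0.8 × √(2/151) = 0.0921. Half-width of the 95% confidence interval = 1.96 × 0.0921 = 0.180.

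**Step 3. Precision with screening SCL-10 in the model.** The residual SD is 0.8 × √(1 − r²), so the variance falls by r². Power = Φ(0.30/SE − 1.96). At r = 0.5, residual SD = 0.693, SE = 0.693 × √(2/151) = 0.0797 and 0.30/0.0797 = 3.76. Then Φ(3.76 − 1.96) gives 96.4%.

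| Assumed r | Variance removed | Residual SD | Half-width | Power at 151 per arm | Total N for 90% power |
|---|---|---|---|---|---|
| not used | 0% | 0.800 | 0.180 | 90.3% | 300 |
| 0.3 | 9% | 0.763 | 0.172 | 92.7% | 272 |
| 0.4 | 16% | 0.733 | 0.165 | 94.5% | 252 |
| 0.5 | 25% | 0.693 | 0.156 | 96.4% | 226 |
| 0.6 | 36% | 0.640 | 0.144 | 98.3% | 192 |
| 0.7 | 49% | 0.571 | 0.129 | 99.5% | 154 |

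(The last two columns use the normal approximation.)

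**Step 4. Does a linear mixed model secure this gain?** It depends on the parameterisation. With complete data at screening and week 16:

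- A model with one common baseline mean for both arms behaves like analysis of covariance. At r = 0.6 its SE is 0.0921 × √(1 − 0.36) = 0.074.
- A model with free arm-by-time means returns, as its week-16 contrast, exactly the difference in week-16 means, with SE 0.092 whatever r is.
- The change-from-baseline contrast of that second model has variance 2(1 − r) times the unadjusted variance. At r = 0.6 its SE is 0.0921 × √0.8 = 0.082. At r = 0.5 it gains nothing, and below that it is less precise than the unadjusted comparison.

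A 200-run simulation at r = 0.6 confirmed the two equivalences. The common-baseline model and analysis of covariance both had an empirical SD of 0.074. The free-means week-16 contrast and the unadjusted difference were identical, both 0.084. With so few runs that 0.084 falls somewhat below the exact 0.092, and the simulated 0.088 for the change contrast lies above its exact 0.082. The formulas, not the simulation, should be used to rank those two.

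**Step 5. Sensitivity to attrition (assumed).** With 20% lost, 120.8 per arm remain. Power is then 83.0% without baseline, against 86.3% (r = 0.3), 92.0% (r = 0.5) or 98.3% (r = 0.7) with it.

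**The case against.** The strongest reply is that the adjustment sentence concerns confounders in sensitivity analyses and does not remove the screening score from the primary model. A linear mixed model on repeated SCL-10 can use that score fully. The article defers model detail to a later analysis plan, which is normal for a published protocol. The trial is sized for an unadjusted comparison, so even that analysis would deliver the planned power, and the article's Discussion mentions blinded analysts.

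Much of this stands, and it rules out three stronger readings:

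- A reader might infer that the primary comparison discards the baseline information. The text does not say so. It leaves the question open, so the precision is not secured rather than given up.
- A reader might infer that the choice of primary analysis hangs on observed imbalance. It does not. The trigger decides only whether, and for which variables, adjusted sensitivity estimates are shown.
- A reader might infer bias or an undersized trial. Neither follows. The unadjusted difference is unbiased under randomisation, 302 reproduces, and with baseline adjustment it would be conservative.

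What does not stand is the appeal to the later plan as a full answer. The imbalance rule is published, not omitted, so a plan that prespecifies adjustment independently of imbalance would have to replace it. Blinding the analysts to arm limits selective adjustment, but imbalance remains the wrong criterion.

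**Conclusion.** The point holds in a limited form. The one adjustment rule the article states is badly fixed: it is triggered by imbalance, has no threshold, names no covariates and is confined to sensitivity analyses. Nothing commits the primary model to a screening score that the trial already collects, and at least one mixed model consistent with the text would gain nothing from it.

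The size of the possible loss is set out in the table, from 9% of the variance at r = 0.3 to 49% at r = 0.7. It rests on two assumptions: a value of r that the article does not give, and a primary model that does not use baseline, which the article neither states nor excludes. The loss is one of efficiency and clear prespecification, not of validity. The change is worth making because it costs nothing and protects power if participants are lost.

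**What to change.** Replace the imbalance sentence in Analyses and statistical methods, and carry the same text into the analysis plan, with:

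> The primary linear mixed model will include screening SCL-10, as a covariate or as a repeated measure with a common baseline mean across arms, whatever the observed imbalance. Each secondary outcome measured at screening will be adjusted for its own baseline value in the same way. No covariate will be selected on observed imbalance. The unadjusted estimate will be reported as a sensitivity analysis.

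The plan should choose one of the two parameterisations before data export. The cost is wording only: Table 1 already schedules the screening measurements, and the sample size need not change.

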### Potential harms and data monitoring

The participants receiving the intervention may experience inferior outcomes compared to the standard treatment. However, this is not considered as likely. Some might have allergies to components within the fruit smoothie, but severe allergies to these are rare, and people with severe allergies who are vulnerable to negative reactions will be excluded from participation in this trial. People with poorly regulated diabetes mellitus type 1 or 2 will be excluded from our trial as these might have needed treatment modifications. The *“therapeutic window”* of fruit smoothie is relatively wide, and except for some experiencing bloating and bowel distension, other side effects are uncommon.

All grade 3 and 4 adverse events are considered Serious Adverse Events (SAEs) and will be reported as such (including anaphylactic reactions). For safety evaluation, all SAEs occurring during the trial follow-up period will be recorded. All SAEs will be followed according to current treatment guidelines until resolution or until a stable clinical endpoint is reached. There is no independent data monitoring committee, but the study coordination unit will ensure protocol adherence, study quality, and ethical conduct. If severe allergic or anaphylactic reactions occur, these will be treated according to the standard protocol for allergic reactions used for anaphylactic reactions to vaccines and medications. A subsequent assessment will include total and fruit-specific immunoglobulins E to evaluate potential links between the intervention and the SAEs.

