**Discussion:**

This study will inform on the relative advantages or disadvantages of fruit supplementation in addition to the current medically and psychologically oriented treatment of people receiving opioid agonist therapy. If the supplementation is efficacious, it can be considered for further scale-up.

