## Background

People with substance use disorders and particularly those with opioid dependence, have high morbidity, reduced quality of life, and a high risk of early mortality [1, 2]. Studies on people with opioid dependence in comparable settings have shown diet patterns with a low intake of fruits and vegetables, reflected in biochemical indicators [3, 4]. Folic acid and carotenoids are among the biochemical markers of intake of fruits and vegetables, and studies show correlations between these biochemical markers and longevity [5]. An inadequate intake of vegetables and fruits could be a risk factor for diseases and early deaths, and an increase in these could have beneficial effects on several health outcomes [5–7]. High consumption of fruits and vegetables is associated with a reduction in cardiovascular disease, cancers, and all-cause mortality.

In the Oslo Antioxidant study, a randomized controlled trial, people smoking tobacco received either kiwi fruits, a combination of various antioxidant-rich foods including fruit smoothies, or none except their habitual regular diet [8]. This study observed changed gene expressions linked with cellular protective mechanisms after an eight-week intervention period with kiwi or antioxidant-rich foods. Another randomized controlled trial among people with chronic obstructive lung disease in Greece showed less progression of lung diseases among those increasing the consumption of fruits and vegetables substantially [9]. Trials have also shown promising findings on psychological distress of healthy diets, including increasing fruits and vegetables in addition to other elements [10, 11]. The impact of fruit smoothie supplementation alone is uncertain, as its potential impact on inflammation [12].

Very few experimental studies focusing on nutrition have been conducted among people with substance use disorders. To our knowledge, there are no other trials having investigated the effects of fruits and vegetables on people with substance use disorders aiming to improve mental health and physical functioning. A recently conducted pilot study by our team with a similar intervention has shown favourable experiences [not yet published]. Thus, we will conduct a multicentre randomised controlled trial to test if daily intake of fruit smoothie over sixteen weeks could improve psychological well-being, physical function tests, and biochemical indicators.

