## Abbreviations

OAT: Opioid agonist therapy
SAE: Severe adverse effects

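### The one stated criterion for a serious adverse event is severity grade, which leaves deaths and lower-grade hospital admissions unclassified, and SAE is expanded in two conflicting ways

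*Protocol article*

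**What the plan says.** The section on potential harms and data monitoring in the protocol article sets the rule: "All grade 3 and 4 adverse events are considered Serious Adverse Events (SAEs) and will be reported as such (including anaphylactic reactions". It then ties safety data to that category: "For safety evaluation, all SAEs occurring during the trial follow-up period will be recorded". Follow-up is stated for the same category: "All SAEs will be followed according to current treatment guidelines until resolution or until a stable clinical endpoint is reached". The section gives no outcome-based criterion such as death, hospitalisation or disability, and it does not say which grading scale is meant. It also states that the trial has no independent data monitoring committee.

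The abbreviation list expands the term differently: "SAE: Severe adverse effects".

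Three other places bear on the point. The Background says that people with opioid dependence "have high morbidity, reduced quality of life, and a high risk of early mortality". The harms section describes the expected tolerability of the smoothie: "except for some experiencing bloating and bowel distension, other side effects are uncommon". The Discussion paragraph of the abstract says the study will inform on the "relative advantages or disadvantages of fruit supplementation".

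**The concern.** Severity and seriousness are different attributes of an event. Severity (grade) describes intensity. Seriousness describes consequence: death, threat to life, hospital admission or its prolongation, lasting disability, or another medically important outcome. A rule that turns grade directly into seriousness misclassifies some events and leaves others without a class.

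The two expansions of SAE add a second ambiguity. An adverse event is anything untoward that happens; an adverse effect implies that the intervention caused it. The control arm receives no smoothie and so can have no smoothie effects. If staff work from the abbreviation list, the arms would not be counted on the same basis.

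What is at stake is the safety comparison between arms. It depends on how each clinic reads the rule, in a population with high early mortality and without an independent committee that would see the pattern.

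**Working it through.** **1. The rule set against the events it has to classify**

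| Event | What the harms section says |
|---|---|
| Grade 3 or 4, with a serious outcome | SAE |
| Grade 3, transient, no serious outcome | SAE, because grade alone is sufficient |
| Anaphylactic reaction | SAE, named explicitly |
| Lower grade, leading to hospital admission | Not assigned |
| Death | Not assigned; on a five-grade scale death is grade 5, but no scale is named |
| Other event below grade 3 (for example mild bloating) | Not an SAE by the stated rule; no recording rule given |

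The second row is over-inclusion and follows directly from the sentence. The fourth and fifth rows are gaps left by silence. The sentence makes grade 3 or 4 sufficient for an SAE; it does not make it necessary.

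**2. The two expansions of SAE**

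| Place | First word | Last word |
|---|---|---|
| Harms section | Serious | Events |
| Abbreviations | Severe | effects |

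Both words that matter differ: one changes the attribute (outcome or intensity), the other changes whether causation is implied.

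**3. How likely is it that the gap matters?**

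Inputs from the article:
- Sample size 302, 151 per arm. A two-sided t-test with difference 2.2 − 1.90 = 0.3, SD 0.8, alpha 5% and power 90% needs 150.4, so 151 per arm. The stated figure reproduces.
- Follow-up: a 16-week intervention, then a visit 10 to 30 weeks after completion, so 16 + 10 = 26 to 16 + 30 = 46 weeks.

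Assumed input: annual mortality *r* of 1% to 4%. The article calls the risk high but gives no rate.

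Expected deaths over *w* weeks = 302 × [1 − (1 − *r*)^(*w*/52)].

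Probability of at least one death = 1 − (1 − *r*)^(302*w*/52).

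| Assumed *r* | 16 weeks: deaths, P(≥1) | 26 weeks: deaths, P(≥1) | 46 weeks: deaths, P(≥1) |
|---|---|---|---|
| 1% | 0.93, 0.61 | 1.51, 0.78 | 2.67, 0.93 |
| 2% | 1.87, 0.85 | 3.04, 0.95 | 5.35, >0.99 |
| 3% | 2.82, 0.94 | 4.56, 0.99 | 8.03, >0.99 |
| 4% | 3.77, 0.98 | 6.10, >0.99 | 10.71, >0.99 |

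Example: *r* = 1%, 26 weeks: 302 × (1 − 0.99^0.5) = 302 × 0.00501 = 1.51.

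These are all deaths expected in the trial, in both arms together. They are not counts of unreported deaths.

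**The case against.** The strongest reply is that the sentence contains no word such as *only*. It says that every grade 3 or 4 event is an SAE, not that nothing else is. A reader might infer that deaths and lower-grade admissions are excluded, but the article does not support that. It also takes an unnamed five-grade scale to place death outside grades 3 and 4, and it assumes that staff would not report a fatal event under a rule meant to catch severe ones.

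A reader might also infer that bloating and other mild effects would go unrecorded. That too goes further than the text. The article says SAEs will be recorded; it does not say other events will not be. It lists follow-up by clinic staff during weeks 0 to 16 and a clinical assessment at week 16 without giving the content of the forms. An article condenses a full protocol, where the seriousness criteria, the grading scale and the collection of non-serious events may well be set out. The abstract's general aim of weighing advantages and disadvantages is not a promise to tabulate tolerability.

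Finally, the intervention is a marketed food, allergy and poorly regulated diabetes are exclusions, and the article calls the trial low-risk.

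All of this stands as a limit on the point. It does not remove it. The article goes beyond silence: it states a rule, and that rule equates grade with seriousness. Over-inclusion of grade 3 events needs no inference. The conflict between the harms section and the abbreviation list is on the page, whatever a fuller document contains.

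**Conclusion.** The point holds as one about definition and consistency. The only SAE criterion stated is a severity grade on an unnamed scale, recording for safety evaluation is stated for SAEs alone, and the two expansions of SAE conflict. Every grade 3 event counts as serious, and deaths and lower-grade admissions have no stated class.

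Its size cannot be measured from the article. At assumed mortality of 1% to 4% a year, at least one death is more likely than not within 16 weeks (probability 0.61 to 0.98), so the classification will probably be tested. Those figures rest wholly on the assumed rate and on all 302 participants being followed for the stated time.

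The change is worth making because it is cheap and the population is at high risk. It has no bearing on alpha or on the efficacy analysis.

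**What to change.** - Define an SAE by outcome: death, life-threatening event, hospitalisation or its prolongation, persistent disability, or another medically important event, including anaphylaxis.
- Apply the definition in both arms from randomisation, whatever the presumed cause.
- Report severity grade as a separate item, on a named scale.
- Bring the abbreviation list and the harms section to one expansion of SAE.

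If the full protocol already does this, only the article's wording needs correcting. Otherwise the cost is protocol wording, a field on the case report form and slightly more reporting work. A question on gastrointestinal tolerability at the existing week-16 visit, asked in both arms, would be a useful extra but is not needed to resolve this point.
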